**Abstract**

Traumatic events, such as traffic accidents, assaults and rapes, are unfortunately common phenomena in the population. Typical reactions for victims are flashbacks, increased anxiety and depressive symptoms. These symptoms usually disappear within a few months after the event, but for about 20%, these symptoms may develop into post-traumatic stress disorder (PTSD).

Although PTSD is relatively common, only a fraction of sufferers are detected by the health care system and detected cases are often left without proper treatment. PTSD is associated with increased risk of suicide and sick leave, and preventive work is clearly needed to lower the incidence of this disorder. Critically, as PTSD is the only mental health disorder where we have a known onset event, we should seize the opportunity to prevent the buildup of potentially long-standing symptoms.

Trauma Focused Cognitive-Behavior Therapy (TF-CBT) is the most promising intervention for preventing PTSD. TF-CBT is provided directly at the hospital emergency room, and has been shown in one trial to decrease the incidence of later PTSD. However, this recent and promising study acknowledged several limitations such as a small sample size, short follow-up time and lack of proper monitoring of treatment side effects.

In light of this, we propose a large-scale randomized trial (n=352), where patients attending an emergency room and have experienced a traumatic event are randomized to either TF-CBT or treatment-as-usual. We will measure PTSD symptoms, quality of life, treatment side effects, process data as well as health economic data up to 10 years.

If TF-CBT is found to be effective, it would mean that we can intervene on PTSD before it develops and we would have valuable knowledge about it´s cost-effectiveness and on the biological and psychological mechanisms that are at play. This would be of immense importance to the millions of people worldwide who will experience inevitable future accidents and traumatic events.

Introduction

**1 ABOUT POST-TRAUMATIC STRESS DISORDER**

1.1 PREVALENCE AND CLINICAL FEATURES

About 51-61% of the general population will experience a traumatic event at some point in their life (e.g. traffic accident, assault or rape).[^1^](#_ENREF_1) Typical reactions after a trauma are intrusive memories of the event, flashbacks, and depressive symptoms.[^2^](#_ENREF_2) These symptoms usually disappear within a few days or weeks after the event, but for about 20%, these symptoms develop into post-traumatic stress disorder (PTSD).[^3^](#_ENREF_3) PTSD is a mental disorder and means that the person who was exposed to trauma still re-experiences this traumatic event through intrusive memories at least one month after the event and these symptoms cause clinical significant distress.[^1^](#_ENREF_1)

PTSD is a detrimental condition for the sufferer and is associated with increased risk of suicide, drug- and alcohol dependence and sick leave.[^4^](#_ENREF_4) Additionally, PTSD-patients show increased somatic problems including both neurological-, vascular-, respiratory-, gastrointestinal and autoimmune diseases.[^5^](#_ENREF_5) PTSD is relatively common in Sweden with a life-time prevalence of 5.6%[^6^](#_ENREF_6) and recent numbers have shown that as much as 20-30% of the patients at the emergency trauma care at Karolinska Hospital, Stockholm, have clinical symptoms that warrants treatment.[^7^](#_ENREF_7) Thus, this is a serious societal problem.

1.2 TREATMENTS

The current psychological treatment for PTSD with best empirical support is Trauma Focused Cognitive-Behavior Therapy (TF-CBT). Briefly, in TF-CBT symptoms of PTSD are seen as signs of an incompletely processed memory, and that the memory is associated with high levels of fear and stress, which in turn drive avoidance behaviors that prevent the person from facing their memories and overcoming their problems. Thus, in TF-CBT the patient re-activates the memory repeatedly in a safe and non-stressful context (i.e., visualizes the event in their mind’s eye several times) for the fearful responses associated to the memory to gradually decline. As a consequence, the flashbacks and intrusions disappear. TF-CBT consists of 15 sessions that is focused on this process i.e. that the patient exposes him/herself to the fear memory and stay in that memory until the fear response is extinguished. TF-CBT for PTSD has been investigated in numerous trials with overall large effect sizes and remission rates averaging 55%-75%.[^8^](#_ENREF_8) Pharmacotherapy has also been tested in several trials but with substantially lower effect sizes compared with TF-CBT.[^9^](#_ENREF_9)

1.3 CURRENT BARRIERS TO TREATMENT

Despite the fact that PTSD is common, only a fraction of the persons suffering from this disorder are detected by the health care system. One example of this is the study by Al-Saffar where 115 psychiatric patients were interviewed and screened for PTSD. The authors found that about 20-30% of the psychiatric patients in this sample fulfilled the diagnostic criteria of PTSD, but none of them had actually received a PTSD-diagnosis from their physician.[^10^](#_ENREF_10) Additionally, although effective treatments for PTSD exist, many patients that are detected are still often left without proper treatment. In Sweden, less than 20% of clinicians use evidence based psychological treatment in their regular practice for PTSD.[^11^](#_ENREF_11) Thus, given the societal burden associated with PTSD and the problems with both detection and treatment, we clearly need to find alternative ways to lower the prevalence of this disorder.

1.4 THE POSSIBLE SOLUTION

The traditional psychiatric research paradigm has been to investigate the efficacy of a treatment package for patients who suffer from an already developed mental health disorder. Although this approach have been partly successful and helped a lot of patients, we have still not managed to substantially decrease the prevalence of any mental disorder.[^12^](#_ENREF_12)^,^[^13^](#_ENREF_13) An alternative approach here would instead be to develop preventive interventions i.e. to intervene on the disorder before it develops. Preventive care has been successful in physical medicine (e.g. cancer- or heart disease- research)[^12^](#_ENREF_12)^,^[^13^](#_ENREF_13) but has lagged considerably behind in the mental health field. As PTSD is the only mental health disorder where we have a known onset event, it is an obvious candidate for preventive interventions.

**2 PREVENTIVE INTERVENTIONS FOR PTSD**

2.1 PREVIOUS RESEARCH

There have been several attempts the last decade to pharmacologically intervene on PTSD before it develops. Four trials have found that early administration of hydrocortisone can make a small preventive effect but these trials also suffered form several methodological limitations. Other pharmacological have shown disappointing results.[^14^](#_ENREF_14)

For psychological treatments, only one intervention has so far proven to be effective in preventing the development of PTSD. This intervention is a shortened version of TF-CBT and is provided directly at the hospital emergency department about 12-24 hours after the trauma. This treatment is only 3 sessions long and is administered within a couple of weeks after experiencing trauma. The main point of giving TF-CBT acutely is to modify fear memories before they go through extensive consolidation during sleep cycle, thereby preventing the onset of PTSD.[^15^](#_ENREF_15) One recent randomized trial by Rothbaum et al. pilot tested this shortened version of TF-CBT on 137 trauma care patients (treatment was given at the emergency department) and found that this intervention indeed managed to decrease the incidence of later PTSD.[^16^](#_ENREF_16)

2.2 REMAINING RESEARCH QUESTIONS THAT NEED TO BE ANSWERED

Preliminary results from the Rothbaum et al. study are encouraging as it is the first study that has managed to show clinically meaningful effects in preventing PTSD. However, this study also experienced several limitations and there are still several research gaps that need to be filled. Below are the current research questions that are critical to answer in order to take the next step and implement TF-CBT in regular emergency care.

2.2.1 IS TF-CBT AN EFFICATIOUS AND SAFE TREATMENT IN PREVENTING PTSD?

One major limitation with the Rothbaum et al. trial was that it used a relatively small sample size (n=137) and this may question the reliability of the results. It is important to note that in these settings a sizeable portion of the participants will recover spontaneously and larger samples are needed as compared to treatments of chronic patients. Another limitation in their study was the short follow-up time of 12 weeks. This is problematic both from a scientific view as well as for policy makers because we do not know how this treatment stands in a 6- or 12-month period. Furthermore, the Rothbaum study also lacked systematic data collection on potential side effects that were associated with the treatment. This is an important issue as one psychological intervention for PTSD (i.e. “Debriefing”) has actually shown worsening of symptoms compared to treatment-as-usual.[^17^](#_ENREF_17) Thus, we need to do a large-scale trial with longer follow-up assessments and close monitoring of adverse events .

2.2.2 IS TF-CBT A COST-EFFECTIVE TREATMENT IN PREVENTING PTSD?

Another limitation with the Rothbaum et al. study was the lack of a health economical evaluation. From an implementation perspective, this is an important issue as policy makers need to know how much benefit an intervention do in relation to the costs associated with the intervention. Cost-effectiveness research has received increasing interest the last decades but lacks considerably behind in both psychiatric- as well as psychological science.[^18^](#_ENREF_18) Thus, one critical aspect here is to find out how much societal gains TF-CBT provides in relation to the economical costs.

2.2.3 HOW DO WE ACHIEVE SUCCESSFUL OUTCOME IN TF-CBT?

One final limitation with the Rothbaum et al. study was the lack of investigation of hypothesis driven underlying mechanisms. Revealing the mechanisms of psychological treatments are imperative in order to move the field forward.[^12^](#_ENREF_12)^,^[^13^](#_ENREF_13)^,^[^19^](#_ENREF_19) Thus, the key and also novel area that needs more research is about mediators of treatment response – that is the underlying mechanisms.

TF-CBT is based on “emotional processing theory” which stipulates that, in order to achieve complete emotional processing, the patient needs to a) active the fear memory (initial fear activation), b) stay in the fear memory until the fear subsides (within-session habituation) and c) repeat this procedure until the memory is no longer associated with fear (between-session habituation).[^20^](#_ENREF_20) Although previous studies have shown support for this pathway (i.e. initial fear activation 🡪 within-session habituation 🡪 between-session habituation 🡪 lower PTSD symptoms),[^20^](#_ENREF_20) it has never been tested within a preventive context.

Data on treatment mediators is important because it would provide us with knowledge of how the treatment achieves its effects. For instance, if patients who do not succeed with initial fear activation 🡪 within-session habituation 🡪 between-session habituation would have worse treatment response, it would mean that we could increase the amount of support for these patients and maximize the treatment dose. In addition, research is also lacking on other emotions such as disgust, not-just-right emotions or shame/anger.[^21^](#_ENREF_21) Research about this would not only give us better treatment effects but, even more importantly, it would give us new knowledge about psychological reactions and how to manipulate memory consolidation in the immediate aftermath after experiencing trauma.

**3 THE NEXT RESEARCH STEP**

Our research group has completed over 20 randomized controlled trials (both psychological and pharmacological treatments) for different mental health disorders. These trials have all followed a classical psychiatric outline i.e. investigate the efficacy of a treatment package for patients who suffer from an already developed mental health disorder. However, the next logical step is now to 1) create preventive treatments, 2) understand how these treatments work in terms of mechanisms and 3) gain knowledge for whom does it work for. This focus on process research and exploring the psychological and biological mechanisms has also recently been pointed out by the US national institute of mental health (NIMH) in the new “research domain criteria” (RDoC).[^12^](#_ENREF_12)^,^[^13^](#_ENREF_13)

3.2 OUR GENERAL AIM

We see a need for research on TF-CBT as a preventive treatment along as well as to extend this well-defined treatment paradigm to investigate mediators of treatment response and biomarkers, with additional analyses on health economical aspects. As pointed out by the chief director at NIMH in a recent paper in JAMA Psychiatry,[^12^](#_ENREF_12) focus on mediators is especially important as it allows a trial to be informative even if the intervention would not show any incremental effects i.e. we can investigate if we were able to affect the mediator and if the mediator in turn affected the outcome.

**4 PURPOSE OF THE STUDY**

Prevention of stress symptoms after a traumatic event is a major goal for psychological treatment innovation and science alike. The main purpose of this study is to test if TF-CBT provided soon after trauma at a Hospital emergency department can be effective in decreasing the incidence of PTSD. We also want to investigate the active psychological and biological mechanisms that are underlying this intervention.

4.1 RESEARCH QUESTIONS

1. Is TF-CBT an effective treatment in preventing the development of PTSD symptoms?
2. Is TF-CBT a cost-effective treatment in preventing the development of PTSD symptoms?
3. What are the mediators of treatment response; i.e. the underlying psychological and biological mechanisms?

Methods

**1. IS TF-CBT AN EFFECTIVE TREATMENT IN PREVENTING THE DEVELOPMENT OF PTSD SYMPTOMS?**

1.1 OVERALL DESIGN AND PROCEDURE

The design is a randomized controlled trial, where patients in the emergency department who have experienced a traumatic event according to the A-criteria in the DSM-5 (e.g. car crash, rape), are randomized to receive either TF-CBT or to placebo. The placebo group will receive basic written information about PTSD and how treat these symptoms. Thus, the rationale for the placebo arm is to provide the patient with a sham treatment to rule out any major placebo effects. Given the estimated effect sizes in the previous trial by Rothbaum et al. we would need 352 patients (176 in each group) in order to detect a standardized effect size (Cohen´s *d*) of 0.3 (*p* = .05, 80% power). We also want to include additional 10 participants in the beginning of the trial just to test the study procedures.

Exclusion criteria are the following: a) Do not want to participate in the study, b) Ongoing intoxication (e.g. due to alcohol), c) Low cognitive capacity, d) Other serious psychiatric comorbidity (ongoing psychotic symptoms or symptoms from bipolar 1, suicidal ideation)

We will screen all trauma patients at Traumacentrum Karolinska (about 1500 patients per year). Psychiatric interviews will be conducted by a licensed psychologist at the emergency department or any related clinic (e.g. if the patient has been transferred to another clinic). Patients who fulfill the A-criterion in DSM-5 (i.e. they have experienced a highly stressful event threatening physical or psychological integrity) will be asked to participate in the study. Informed consent will be delivered both as written text as well as explained by the study personnel. Baseline assessments (shown below) will then be conducted.

After the patients have signed the informed consent and completed the baseline assessments, they are randomized to either TF-CBT or placebo. Block randomization will be done beforehand by an independent party (Karolinska Trial Alliance; KTA) on an 1:1 ratio.

Participants randomized to TF-CBT will receive a brief 3-session intervention provided within 72 hours after the accident. In this treatment, the patient is instructed to systematically expose him/herself to the fearful memory of the event and stay in this memory until the anxiety has attenuated. By doing this exposure repeated times, the association between the memory and fear response is hypothesized to be gradually extinguished. The placebo group will receive sham treatment i.e. written information about PTSD and how to treat it but without any therapist-guided interventions.

We will measure PTSD symptoms using the Clinician Administered PTSD Scale (CAPS; the gold standard for PTSD assessment) and Posttraumatic Diagnostic Scale,[^22^](#_ENREF_22)^,^[^23^](#_ENREF_23) depression using the Montgomery Åsberg Depression Rating Scale – Self rated (MADRS-S),[^24^](#_ENREF_24) quality of life using the EQ-5D[^25^](#_ENREF_25) and treatment side effects using the Safety Monitoring Uniform Report Form (SMURF)[^26^](#_ENREF_26) at baseline (i.e. before treatment allocation), 2-, 6-, 12-, 24-, 48- and 120 months using blinded assessors. Primary endpoint is set to 6-months after the trauma. Patients unable to come to the clinic for follow-up assessments will be interviewed via telephone or skype.

The primary outcome (significant PTSD symptoms assessed by the CAPS) will be analyzed using risk ratios and numbers-needed-to-treat with 95% confidence intervals. Continuous data will be analyzed in a mixed-effects model adjusting for data attrition (covariance and residual structure will be set based on the best model fit of the data) using intention-to-treat design. Effect sizes for continuous measures will be estimated using Cohen´s *d*. Assessor´s blindness will be also tested (each assessor will guess treatment allocation for each participant and this will be tested in a logistic regression with guess as independent variable and allocation as dependent variable). A flowchart of the treatment study is shown in the attached figure.

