2.3 COST-EFFECTIVENESS ANALYSES

Cost-effectiveness comparisons will be analyzed using incremental cost-effectiveness ratios as well as the net benefit approach with different willingness-to-pay scenarios. Cost-effectiveness ratios are calculated as following: (Δ^C1^ – Δ^C2^)/(Δ^E1^ – Δ^E2^), where Δ^C1^ – Δ^C2^ is the difference in cost change (from pre- to follow-up) between the two treatment groups. Δ^E1^ – Δ^E2^ refers to the corresponding difference in clinical outcome (i.e. PTSD vs. no PTSD). Because cost-effectiveness is a relative term i.e. an intervention is only cost-effective depending on how much the society is willing to pay for one unit of improvement, we will also use the ”net benefit approach”, which estimates the cost-effectiveness depending on different societal willingness-to-pay values for one unit of improvement. The net benefit of each individual in this trial will be calculated according to the following formula: (λ x E) – Δ^C^ where λ is the willingness to pay (i.e. the different values that the society is willing to pay for one unit of improvement), E is the efficacy (i.e. PTSD status or gain on the EQ-5D), and Δ^C^ is the cost change from baseline to primary endpoint (6-months). We will calculate individual net benefits by assuming different values for λ and a regression model with non-parametric bootstrapping (one thousand replications) to estimate be difference between TF-CBT treatment-as-usual. Cost-effectiveness acceptability curves will be used to get a visual estimate of the total net benefit of TF-CBT.

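### The control arm carries conflicting names, and written information without therapist contact cannot support the stated aim of ruling out placebo effects

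*Protocol*

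**What the plan says.** The Protocol names the control arm in two incompatible ways.

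- **Treatment-as-usual.** In the Abstract, patients "are randomized to either TF-CBT or treatment-as-usual". In Methods 2.3, the net-benefit regression is meant "to estimate be difference between TF-CBT treatment-as-usual".
- **Placebo and sham.** In Methods 1.1, patients "are randomized to receive either TF-CBT or to placebo", and after consent and baseline "they are randomized to either TF-CBT or placebo".

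The content of the arm is given twice in Methods 1.1, consistently: "The placebo group will receive basic written information about PTSD and how treat these symptoms", and later "The placebo group will receive sham treatment i.e. written information about PTSD and how to treat it but without any therapist-guided interventions". The purpose is also stated there: "the rationale for the placebo arm is to provide the patient with a sham treatment to rule out any major placebo effects".

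The TF-CBT arm receives three sessions (Methods 1.1), and a psychologist guides each exposure session (Methods 3.1). Methods 1.1 lists the CAPS, the Posttraumatic Diagnostic Scale (PDS), the MADRS-S, the EQ-5D and the side-effect form together, and says of all of them that blinded assessors are used.

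**The concern.** Treatment-as-usual and a placebo or sham are different comparators. The first is whatever patients would have received anyway. The second is meant to reproduce the non-specific parts of treatment, so that a remaining difference can be credited to the specific ingredient. A document that uses both names leaves the reader unsure which claim the trial will make.

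The placebo name brings a causal claim with it. If the result is reported as placebo-controlled, readers will take it that expectancy and similar influences have been excluded. The design as described does not exclude them. At stake is how a positive result may be worded, in a study that Scientific implications presents as definitive, and how the comparator is labelled in the economic results.

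**Working it through.** **1. The plan's own figure.** Inputs from Methods 1.1: d = 0.3, alpha 0.05 (sidedness not stated; two-sided assumed), power 80%, 1:1 allocation.

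n per arm = 2(z₀.₉₇₅ + z₀.₈₀)² / d² = 2 × (1.9600 + 0.8416)² / 0.3² = 2 × 7.849 / 0.09 = 174.4, so 175 per arm and 350 in total.

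The t-test version gives 175.4, rounded up to 176 per arm, or 352 in total. Power at 176 per arm is 80.1% (t) or 80.4% (normal). The stated 352 is reproduced, and nothing below depends on it.

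**2. The names.** Treatment-as-usual is applied to this trial's control in two places, the Abstract and Methods 2.3. The same term in Introduction 2.2.1 and in Ethical considerations refers to debriefing studies and is not counted. Placebo and sham wording recurs throughout Methods 1.1. No section describes usual care or says whether it accompanies the written information.

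**3. What differs between the arms.**

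| Component | TF-CBT | Control | Balanced? |
|---|---|---|---|
| Psychologist interview and baseline assessment | yes | yes | yes |
| Follow-up assessments | same schedule | same schedule | yes |
| Blinded rating of the CAPS | yes | yes | yes |
| Exposure to the trauma memory | yes | no | no (intended) |
| Psychologist-led sessions | 3 | 0 | no |
| Patient sees what was delivered | sessions | written material | no, so expectancy can differ |

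Let S be the effect of exposure itself, N the effect of therapist contact, attention and expectancy, and W the effect of the written information. Assume for simplicity that effects add and that the TF-CBT arm does not also receive the written material. The trial then estimates

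S + N − W.

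Ruling out placebo effects would require N to be matched in the control arm, leaving S. It is not matched. W is not known to be zero either, because the material includes advice on treating the symptoms. One contrast cannot identify three terms.

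**4. Whether other parts of the plan separate S from N.**

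- Blinded assessors limit bias in rating. They do not equalise what patients received or expected.
- The planned test of blindness concerns the assessors' guesses, not the patients'.
- Methods 1.2.1 covers envelopes and access to codes. It describes no means of keeping participants unaware.
- The process data for the path analysis (Methods 3.1 and 3.2) come from the exposure sessions. The control arm has none.
- No measure of credibility or expectancy is described.

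**5. Who rates what.** The CAPS is clinician-administered. The MADRS-S is self-rated by its own name, and the reference cited for the PDS describes it in its title as a self-report measure. For these two the patient is the rater, and patients can tell whether they had sessions. How the EQ-5D is completed is not stated.

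**The case against.** The strongest reply is that little turns on the label. The content of the control is described twice, in the same way. The treatment-as-usual wording is one sentence in the Abstract and one garbled clause in Methods 2.3. Neither changes who is randomized, what they receive or how the primary outcome is analysed. The CAPS with blinded assessors is already primary. Research question 1 asks only whether TF-CBT is effective, and package versus written information answers that. The protocol speaks only of major placebo effects and does not claim to isolate therapist time.

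All of this stands as a limit on the point. It does not rescue the rationale sentence, which asserts a property that the described arm does not have, whether the effects are major or small.

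Four stronger readings are tempting, and the documents do not support them.

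- *A reader might infer that costs and benefits would be credited to the wrong alternative.* Methods 2.1 and 2.3 use the patients of this trial in its two arms. The estimated contrast is the same whatever the comparator is called; only its label is wrong.
- *A reader might infer that contact and attention differ completely.* Both arms share the psychologist interview and the assessments. Contact differs substantially, not wholly.
- *A reader might infer that a set share of the planned d = 0.3 is non-specific.* Any such share needs an assumed value that the documents do not give. The primary outcome is also binary, analysed by risk ratio and number needed to treat, so shares of d do not carry over directly.
- *A reader might infer that the control is usual care with material added.* The text does not say so.

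**Conclusion.** The point holds in two parts. The control is named inconsistently, and the rationale of ruling out placebo effects is not supported by an arm that has written information and no therapist-guided contact. The trial gives a valid randomized estimate, for effectiveness and for cost-effectiveness, of the TF-CBT package against written information. It is not a placebo-controlled estimate.

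No numerical size can be given, because the documents contain no figure for non-specific effects. The consequence is a narrower permissible conclusion, with no change to the randomization, the primary outcome or the sample size.

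The conclusion rests on the protocol as shown. Consent pages are not available, so what patients are told about the two arms cannot be seen. Even so, patients would know whether they had sessions or only written material.

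**What to change.** 1. Use one accurate name for the control, for example written information, in the Abstract, Methods 1.1 and Methods 2.3.
2. Have the sponsor state whether usual care accompanies the written information. The reviewer cannot settle this from the document.
3. Delete the placebo and sham wording and the rationale sentence in Methods 1.1.
4. State that effectiveness and cost-effectiveness conclusions concern the TF-CBT package, including therapist contact, versus written information, and are not placebo-controlled.
5. In the outcome sentence of Methods 1.1, limit blinded assessment to the assessor-rated measures. Label at least the MADRS-S and the PDS as self-report by patients who know their allocation, and state how the EQ-5D is completed.

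The cost is editing only: no added patients, visits or procedures. The one downside is a narrower claim.

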# Scientific implications

This project holds important scientific implications:

First, there is to date only one early stage randomized controlled trial in the USA showing that PTSD can be prevented through TF-CBT. This current study is unique in providing an adequately powered test of the hypothesis using a larger sample size, allowing longer-term follow-up assessments, as well as appropriate monitoring of treatment side effects. In addition, the health economical analyses will reveal how much the society needs to pay for one non-case of PTSD. This study is therefore set to be the definitive trail internationally.

Second, a unique aspect of this clinical research study is that we will examine the underlying mechanisms of the treatment, drawing on work in basic neuroscience and cognitive theory. The intervention is hypothesized to modify the trauma memory, and thus to prevent the development of PTSD symptoms, before any major memory consolidation has taken place (i.e. sleep on night one[^31^](#_ENREF_31)) which would otherwise cement the traumatic memories in a maladaptive way. It would therefore be of great scientific value to see if the stipulated effect of the emotional processing theory, which TF-CBT draws upon, applies within this preventive context in a non-psychiatric sample. We will also investigate the role of different emotions and their consequences in treatment outcome. There is a lot of research on fear extinction but, as many other emotions are involved in PTSD as well as other mental disorders, the next step would also to investigate the role of disgust, shame etc. and see if these emotions follow the same path as fear extinction. Research about emotional memory consolidation and treatment mediators would give us highly valuable information both about the etiology of PTSD, and also information on how to treat PTSD in the most effective way with psychological interventions. If we know how our treatment works optimally, we can implement additional instruments and procedures that ensure that we activate the working mechanisms in this treatment. Critically, this study will also be able to demonstrate whether treatment success (or failure) is contingent on the hypothesized mechanisms. Therefore this study will be among the first to link the basic laboratory work on memory consolidation to an applied real world setting.

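### The 80% power behind 352 patients belongs to a continuous Cohen's d of 0.3 with complete follow-up, not to the binary CAPS primary outcome, for which no control risk, target risk ratio or attrition is stated

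*Protocol*

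**What the plan says.** Methods 1.1 (Overall design and procedure) gives the only sample-size justification: "we would need 352 patients (176 in each group) in order to detect a standardized effect size" (Cohen's "d*) of 0.3 (*p* = .05, 80% power"). Allocation is 1:1. No event rate, risk ratio, risk difference or dropout rate accompanies it.

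The same section then defines the main comparison: "The primary outcome (significant PTSD symptoms assessed by the CAPS) will be analyzed using risk ratios and numbers-needed-to-treat with 95% confidence intervals". It also states that "Primary endpoint is set to 6-months after the trauma". Cohen's d appears separately, for other outcomes: "Effect sizes for continuous measures will be estimated using" that measure. Continuous data go into a mixed model that is meant to deal with attrition, so some loss is expected.

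On how often PTSD occurs, the Abstract says of early symptoms "but for about 20%, these symptoms may develop into post-traumatic stress disorder (PTSD"), and Introduction 1.1 (Prevalence and clinical features) repeats it. Introduction 1.1 also gives 20-30% of trauma-care patients at the recruiting hospital with symptoms that call for treatment. Neither figure is linked to the sample size.

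Scientific implications concludes: "This current study is unique in providing an adequately powered test of the hypothesis using a larger sample size".

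**The concern.** Risk ratios and numbers needed to treat exist only for a yes/no outcome. The cost-effectiveness section (Methods 2.3) confirms this reading by setting PTSD against no PTSD, as does the stated purpose (Introduction 4) of lowering the incidence of PTSD. By the Protocol's own allocation of effect measures, Cohen's d is not the measure for the primary outcome. The sample size therefore rests on a different type of outcome from the one it is meant to serve.

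This matters because a score cut at a threshold carries less information than the score itself. The same underlying treatment effect is harder to detect as a difference in caseness, most of all when cases are a minority. Funders, ethics reviewers and readers of the result would take 80% power to apply to the primary comparison, and nothing in the Protocol supports that. The lack of an attrition allowance adds to the problem, because 6-month follow-up of emergency patients is unlikely to be complete.

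**Working it through.** **Inputs.** From Methods 1.1: 176 per arm, d = 0.3, alpha 0.05, power 80%, 1:1. From Introduction 1.1: about 20%, and 20-30%. Assumptions of this check: two-sided alpha (not stated, but needed to reproduce 352), those background rates used as control risk, and 10% or 20% missing at 6 months.

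**1. Reproduce the stated figure.** Normal approximation: n per arm = 2(1.960 + 0.842)² / 0.3² = 174.4, rounded up to 175. The two-sample t-test gives 175.4, rounded up to 176, hence 352; power at 176 is 80.1%. A one-sided test would need 138 per arm. So 352 is the two-sided t-test size with nobody missing, and its arithmetic is correct.

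**2. Carry d = 0.3 over to caseness.**
- Threshold conversion (a normal score shifted by 0.3 and cut at the case threshold): p₂ = Φ(Φ⁻¹(p₁) − 0.3). For p₁ = 0.20: Φ(−0.842 − 0.3) = Φ(−1.142) = 0.127.
- Logistic conversion: ln OR = 0.3π/√3, so OR = 1.72.

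**3. Power of the two-proportion test.** Power = Φ{[(p₁ − p₂) − 1.960·se₀] / se₁}, where se₀ uses the pooled risk and se₁ the separate risks. For 20% vs 12.7% with n = 176: se₀ = 0.0394, se₁ = 0.0392, so Φ[(0.0732 − 0.0772)/0.0392] = Φ(−0.10) = 46%.

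| Control risk | Conversion | TF-CBT risk | RR | Power, n = 176 | 10% missing, n = 158 | 20% missing, n = 141 | Total N for 80% |
|---|---|---|---|---|---|---|---|
| 20% | threshold | 12.7% | 0.63 | 46% | 42% | 38% | 800 |
| 25% | threshold | 16.5% | 0.66 | 50% | 46% | 42% | 712 |
| 30% | threshold | 20.5% | 0.68 | 54% | 50% | 45% | 654 |
| 20% | logistic | 12.7% | 0.63 | 46% | 42% | 38% | 798 |
| 25% | logistic | 16.2% | 0.65 | 53% | 49% | 45% | 664 |
| 30% | logistic | 19.9% | 0.66 | 59% | 54% | 50% | 578 |

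A Wald test on the log risk ratio, closer to the planned analysis, gives 45-53% (threshold) and 45-58% (logistic) with full follow-up.

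**4. A larger effect.** If TF-CBT halves the risk, power at 176 per arm is 75%, 85% and 92% at control risks of 20%, 25% and 30%, before attrition.

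**5. What 352 patients can detect.** Solving step 3 for 80% power:

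| Control risk | Detectable RR, full follow-up | Detectable RR, 20% missing |
|---|---|---|
| 20% | 0.47 | 0.42 |
| 25% | 0.53 | 0.48 |
| 30% | 0.58 | 0.53 |

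**The case against.** Four points deserve weight.

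- **The percentages are conditional.** A reader might infer that the trial simply has 46-54% power, or that its primary test is a coin flip. The Protocol does not support that. The 20% is PTSD after trauma in general, and the 20-30% is symptoms needing treatment among trauma-care patients. Neither is the rate of the trial's endpoint, whose cut-off is not given, in consenting patients who meet the DSM-5 trauma criterion. At an assumed control risk of 40%, power is 58% (threshold) or 67% (logistic). This objection stands against any unconditional figure. It does not rescue the 80%, which neither conversion reaches.
- **The real effect may be larger.** The Protocol ties its target to the earlier trial's effect sizes, and a halved risk is reasonably well covered. That is true, but the only target it states is d = 0.3.
- **Perhaps 0.3 was meant as Cohen's h.** Then 176 per arm would give about 79-80%. The text says d, and states no pair of risks.
- **The continuous CAPS score could be made primary.** This looks like an easy repair, but it would move the primary outcome away from the stated purpose of reducing the incidence of PTSD, so it is a trade-off for the sponsor and not a correction. Nor is its power after attrition settled. A t-test on completers gives 76% and 71% at 10% and 20% loss, but the planned analysis is a mixed model. With an assumed baseline correlation of 0.5, a baseline-adjusted approximation gives about 87% and 83%. The Protocol gives no correlation.

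**Conclusion.** The point holds as a mismatch between two statements in the Protocol. The calculation of 352 is right for a continuous d of 0.3 with complete follow-up, but it does not justify the primary comparison, which is binary and has no stated control risk, target risk ratio or attrition allowance. This does not depend on any statistical analysis plan.

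The size of the shortfall can only be illustrated. With d = 0.3 carried over to caseness, control risk 20-30%, two-sided 5% and no missing data, power is about 46-54% (threshold) or 46-59% (logistic). With an assumed 10-20% missing it is about 38-54% across both conversions. With a halved risk it is about 75-92% before attrition. Whether the trial is adequately powered for its primary outcome thus depends on an effect and a control risk that the Protocol never states, and the claim in Scientific implications is unsupported as worded.

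**What to change.** Keep the 352 patients and the primary outcome, and change the wording in two places.

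1. Methods 1.1: for the primary comparison, replace the 80% power for d = 0.3 with the risk ratio detectable at 80% power with 352 patients, and state the control risk and 6-month attrition assumed. At control risks of 20%, 25% and 30% that risk ratio is about 0.47, 0.53 and 0.58 with full follow-up, and about 0.42, 0.48 and 0.53 with an assumed 20% loss. The sponsor should substitute its own control risk and attrition where it has better figures. Say that the d = 0.3 calculation applies to the continuous CAPS score, two-sided, before attrition.
2. Scientific implications: qualify the claim of adequate power by naming the risk ratio to which it applies.

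The cost is a less favourable stated figure. No extra patients, visits or changes to the planned analysis are needed.
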